| C.3.3.11 | Emergency patient                                                                                                                                                                                                                                                                                                                                                                                                                   |             |
| C.3.3.12 | Students                                                                                                                                                                                                                                                                                                                                                                                                                            |  |
| C.3.3.13 | Older people                                                                                                                                                                                                                                                                                                                                                                                                                        |             |
| C.3.3.14 | Another situation                                                                                                                                                                                                                                                                                                                                                                                                                   |             |
| C.3.4    | 
INCLUSION AND EXCLUSION CRITERIA
 
Inclusion criteria
 
 
1. Being healthy (not having any known, diagnosed chronic diseases)
 
2. Volunteering to participate in the study
 
 
Exclusion criteria
 
 
1. Presence of orthopedic or neurological disease
 
2. Pregnancy
 
 |                                     |
| C.3.5    | 
CONTROL GROUP
 
Participants to be included in Group 2 and Group 3 will be matched by age, gender and dominant hand with those in Group 1.
                                                                                                                                                                                                                                           |                                     |
| C.3.6    | 
THE PLACE THE RESEARCH WILL BE CONDUCTED AND PERMISSIONS
 
The research will be done in the laboratory of Izmir Katip Celebi University Faculty of Health Sciences, Physiotherapy and Rehabilitation under the permission of the Head.
                                                                                                                                               |                                     |
| C.3.7    | 
DATA COLLECTION TOOLS AND FEATURES
 
Dominant hand preference
                                                                                                                                                                                                                                                                                                                 |                                     |

The Edinburgh Handedness Questionnaire (Oldfield, 1971) will be used to determine the dominant hand preference. In this questionnaire, hand preference used in different activities is questioned. The Turkish version of the questionnaire has been shown to be valid and reliable (Nalcaci, Kalaycioglu, Gunes, & Cicek, 2002).

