|         | 
taken (Treece & Treece, 1982). Based on results from a previous motor imagery training study using physiological measurements (mean and standard deviation of heart rate differences between groups), the sample size of 63 participants per group was obtained using the HyLown sample size calculation software (http://powerandsamplesize.com/). Since there will be three groups in this study, it was determined that 189 participants were needed for a full-scale study. Based on these recommendations in the literature, it was decided that the sample size for this pilot study should be 15 participants per group. The total sample size was planned as 54 participants (18 per group), with the addition of possible losses of 20%.
 
Randomization
 
Participants will be divided into three groups using a simple randomization method based on a single sequence using computer software (https://www.randomizer.org/) by a researcher who will not be involved in evaluation and treatment (Altman & Bland, 1999).
 
Motor imagery training
 
DVDs containing motor imagery instructions will be given to the individuals participating in the motor imagery training. The same content will be made available for download online to participants (control) who wish to do so.
 
Group 1 will be trained in activating kinesthetic motor imagery. Scenarios in this motor visualization training will focus on exercises that require high effort (plank, boxing, jumping, crouching, push-up, etc.). In the motor imagery scenarios of the participants in Group 2, low intensity (relaxation) exercises (breathing exercises, stretching, body awareness exercises, etc.) will be included. Motor imagery training for both groups, 5 days a week, 17 minutes a day. It will be applied for 2 weeks (Schuster et al., 2011).
 |                                     |

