| C.3.3    | 
CHARACTERISTICS OF THE VOLUNTEER GROUP
                                                                                                    |                                     |
| C.3.3.1  | Estimated number of volunteers                                                                                                                                                      | 54                                  |
| C.3.3.2  | Child (under 18 years old)                                                                                                                                                          |             |
| C.3.3.3  | Adult (+18 years old)                                                                                                                                                               |  |
| C.3.3.4  | Woman                                                                                                                                                                               |  |
| C.3.3.5  | Man                                                                                                                                                                                 |  |
| C.3.3.6  | Healthy participant                                                                                                                                                                 |  |

|          |                                                                                                                                                                                                                                                                                                                                                                                                                                     |                                     |

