#### **Applicability (feasibility) of the methods**

The feasibility of the methods (safety, side effects, rate of participant acceptance of applications), the feasibility of a full-scale study (target sample size, dropout rate, participation in targeted sessions) will be examined. The rate of falling out of the study should not be more than 20% and the participation in the sessions should not be less than 70%.

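### The 20% loss allowance is added to the target instead of being taken from those enrolled, so 54 participants at 20% loss leave about 43 evaluable, not 45

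*Protocol*

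**What the plan says.** All the figures are in the protocol. Under Sample size in C.3, after citing a minimum of 12 per group for a pilot and a rule of 10% of a full-scale study, it concludes that "it was decided that the sample size for this pilot study should be 15 participants per group". The next sentence gives the enrolment: "The total sample size was planned as 54 participants (18 per group), with the addition of possible losses of 20" per cent. C.3.3.1 ("Estimated number of volunteers") repeats 54.

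Two other places bear on what a 20% loss means. Under the feasibility heading in C.3.7, the protocol sets its own ceiling: "The rate of falling out of the study should not be more than 20" per cent. C.3.9 limits the intention-to-treat analysis to participants who have follow-up data, so each person lost to follow-up reduces the number analysed.

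**The concern.** An allowance for losses is meant to ensure that the intended number remains once the expected share of enrolled participants has gone. Adding 20% to the target does not do this, because the 20% is then lost from the larger enrolled number. The stated 54 therefore does not follow from the stated 15 per group and 20% loss. At stake is whether the protocol describes correctly what its enrolment delivers. The same percentage is also the feasibility ceiling for dropout, so a reader will expect the pilot to reach its planned size when dropout is at that ceiling.

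**Working it through.** **Inputs**

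- Target per group: 15 (C.3, Sample size).
- Groups: 3 (same paragraph), so the total target is 15 x 3 = 45.
- Loss allowance: 20% (same paragraph).
- Planned enrolment: 18 per group, 54 in total (same paragraph; C.3.3.1).
- Dropout ceiling: 20% (feasibility heading in C.3.7).
- Cited pilot minimum: 12 per group (C.3, Sample size).

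**Reproducing the protocol's figure**

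n x (1 + d): 15 x 1.20 = 18 per group; 45 x 1.20 = 54 in total. This matches exactly.

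**What 54 leaves at 20% loss**

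n x (1 - d): 18 x 0.80 = 14.4 per group; 54 x 0.80 = 43.2 in total. Against 15 and 45, the expected shortfall is 0.6 per group and 1.8 in total.

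**Loss rate at which the target still holds**

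(18 - 15)/18 = 3/18 = 16.7% per group; (54 - 45)/54 = 9/54 = 16.7% overall.

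**Enrolment that would keep 15 at 20% loss**

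n/(1 - d): 15/0.80 = 18.75, rounded up to 19 per group, or 57 in total. Check: 19 x 0.80 = 15.2 and 57 x 0.80 = 45.6.

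**In whole people, within the 20% ceiling**

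- A group of 18 can lose 3 (16.7%) and keep exactly 15. A fourth loss is 4/18 = 22.2%, above the ceiling.
- All 54 can lose 10 (10/54 = 18.5%) and keep 44, one short of 45. An eleventh loss is 11/54 = 20.4%, above the ceiling.

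**Chance of keeping the target**

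Assume equal groups and that each participant is lost independently with probability 0.20. The protocol does not state the independence.

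| Enrolled | Target kept | Probability |
|---|---|---|
| 18 in a group | at least 15 | 0.50 |
| 54 in total | at least 45 | 0.34 |
| 19 in a group | at least 15 | 0.67 |
| 57 in total | at least 45 | 0.65 |

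Under the same assumption, a group of 18 keeps at least the cited minimum of 12 with probability 0.95.

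**The case against.** The strongest reply is that the text describes what was done. It speaks of adding 20%, three people are 20% of 15, and 15 + 3 = 18. It nowhere promises 15 evaluable after losing 20% of those enrolled. This is a fair reading of the sentence. But three lost from 18 is a 16.7% loss, and a dropout rate such as the one in the feasibility criterion is most naturally a share of participants enrolled. On that basis the allowance and the ceiling do not match.

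The second reply is about size, and it stands. The 14.4 is an expectation, not a count that can occur. A single group of 18 that stays within the ceiling keeps 15, and the whole trial falls short by at most one person. One group could still lose more than three while the overall rate stays at or below 20%. Simple randomisation, if group sizes are left free, adds more variation than this: the standard deviation of a group's size would be sqrt(54 x 1/3 x 2/3) = 3.5.

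Two stronger readings are tempting, and the protocol supports neither.

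- **The pilot is underpowered.** The 15 comes from rules of thumb, not from a power calculation, so no stated power is lost.
- **The full-scale figure is also wrong.** A reader might infer this from "it was determined that 189 participants were needed for a full-scale study", because 189 is 63 x 3 with no loss allowance and no visible adjustment for three groups. The paragraph does not give the significance level, power, mean difference or standard deviation behind the 63, so whether it is an unadjusted two-group figure cannot be tested. The 189 is stated only as the number needed, and dropout is something the pilot is to examine for the full-scale study.

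**Conclusion.** The point holds as a minor arithmetic correction. Enrolling 54 leaves 43.2 evaluable on average at 20% loss, against 45 planned, and secures 15 per group only up to 16.7% loss. This takes the 20% as a share of those enrolled, 15 per group as the number wanted for analysis, and groups of 18 as planned. The total shortfall of 1.8 does not depend on how the groups fall out. No power statement or decision rule in the protocol changes, and the expected evaluable number stays above the cited minimum of 12 per group. The conclusion does not extend to the full-scale 189.

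**What to change.** In C.3, Sample size, keep 54 and state what it delivers: about 43 evaluable in total if 20% of those enrolled are lost, and 15 per group only while loss is no more than 3 of 18 (16.7%). This is a change of one sentence and needs no further participants.

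If the investigators want 15 per group to hold at 20% loss, the figure is 19 per group, 57 in total, entered in both C.3 and C.3.3.1. That costs three more healthy volunteers and their assessments. Either is adequate for a pilot of this kind.

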|     | 
Duhamel, 2001). Motor imagery can also be defined as implicit or explicit (de Vries et al., 2013). Explicit motor imagery is defined as a phenomenological experience in which the sense of movement is experienced consciously (de Vries et al., 2013). That is, the individual is aware that he is imagining movement. On the other hand, implicit motor imagery is defined as unconscious visualization of movement (de Vries et al., 2013). For example, when an individual looks at a photograph of a hand standing in a different position than normal, he unwittingly imagines his hand gestures moving the hand to the position he is used to and decides whether the hand in the photograph is right or left. Open and closed motor visualization describe different aspects of cognitive task and should not be considered as separate situations from each other. A motor imagery task can be performed both visually and off, kinesthetic, and open, or vice versa (McInnes, Friesen, & Boe, 2016). However, motor imagery tasks used in neurorehabilitation are mostly explicit motor imagery, utilizing both kinesthetic and visual motor imagery (McInnes et al., 2016).
 |
| C.2 | 
RATIONALE/PURPOSE OF STUDY
 
Most of the studies on motor imagery attribute its mechanism of action to neuroplastic changes occurring in the brain (Gerardin et al., 2000; Kraeutner et al., 2014; Mulder, 2007; Schieber, 2013). On the other hand, it is thought that motor imagery can alter metabolic responses, just like in real exercise. In a study conducted on this subject, it was reported that physiological changes such as heart rate, oxygen consumption, blood pressure, respiratory rate, metabolic rate after motor imaging were like actual exercise (Wang & Morgan, 1992). However, the level of evidence for the effect of motor imagery on autonomic functions is extremely limited.
 
The aims of this study are;
 
 
1. To examine the effects of the activating and relaxing kinesthetic motor imagery training program on autonomic functions in healthy individuals and to compare these two methods with each other.
 
2. In the study, the effects of the mentioned training program on the motor imagery skills of individuals will also be examined.
 
  |

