| C.3.8 | 
OPERATIONS AND VARIABLES TO BE USED IN THE RESEARCH
 
In this study, participants will be randomly assigned to one of three groups: Group 1: activating kinesthetic motor imagery training; group 2: relaxing kinesthetic motor
                                                                                                                                                                                                                                                                                                                                                                                                                                                                                                                                                                                                                                                                                                                                                                                                                                                                                                                                                                                                                                                                                                                                                                                                                                                                                                                                                                                                                                                                                                                                                                                                                                                                                                                                                                                                                                                                                                                                                                                                                                                                                                                                                                                                                                                                                                                                                                                            |

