
imagery training; and group 3: control group. After randomization and before the implementation, participants will be given an introductory training to become familiar with motor imagery. The concept of motor imagery and its uses in sports and rehabilitation will be explained. Different types of motor imagery (kinesthetic and visual) and perspectives (inner, first-person and outer, third-person perspective) will be explained theoretically and practically. Participants will be encouraged to practice on their own and be made aware of their preferred type and perspective of motor imagery. Emphasis will be placed on the use of internal and kinesthetic motor imagery in this study. Introductory training before motor image training is recommended by various authors (Schuster et al., 2011; Wondrusch & Schuster-Amft, 2013).

The PETTTLEP framework strategy based on a neuroscientific basis will be used for motor imagery. This strategy consists of Physical, Environmental, Task, Timing, Learning, Emotional and Perspective components (Holmes & Collins, 2001). PETTTLEP is a method developed to increase performance in athletes (Holmes & Collins, 2001). PETTTLEP elements include the practitioner's physical position according to the motor visualization task and perspective, the imagined environment, the imagined task, the timing of the motor imagery, learning or changes with motor imagery, and emotional states. PETTTLEP ideas will be applied in this pilot study to support participants' understanding of the application and effectiveness.

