After the familiarization training and verbal instructions, the participants will be given DropBox links containing engine visualization training videos specially designed for their groups. Participants will be able to download the engine imagination training videos and instructions and watch them on their smartphones, computers, or tablets via these links. Participants will be asked to apply the kinesthetic motor imagery training at their own homes, 5 times a week, once a day for 17 minutes. The videos will be used to enable participants to see the exercises to accurately visualize the relevant movements. The frequency and duration of motor imagery sessions were decided according to the results of a review examining motor imagery training applied in different disciplines (Schuster et al., 2011). After a week, the participants will be called by phone, support will be provided for the application and will be reminded that there will be a post-implementation evaluation. The frequency of the application will be recorded in their exercise logs and they will be asked to report it on the phone. However, there will not be a direct exercise follow-up. Participants in the control group will not be given a special application but will be called by phone to remind the time of the second evaluation.

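### Controls may download the training content with no timing limit, against the protocol's own control condition, so the comparisons with control can be biased

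*Protocol*

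**What the plan says.** Three parts of the protocol bear on what Group 3 receives.

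- **C.3, Motor imagery training.** After saying that the imagery participants receive DVDs, the text adds: "The same content will be made available for download online to participants (control) who wish to do so". It sets no date or condition for this access and does not say whether the activating programme, the relaxing programme or both are meant.
- **C.3.8, on controls.** "Participants in the control group will not be given a special application"; their only described contact is a telephone reminder of the second evaluation.
- **C.3.8, on the introductory session.** Directly after the three groups are listed, control included, the text reads: "After randomization and before the implementation, participants will be given an introductory training to become familiar with motor imagery". It continues: "Participants will be encouraged to practice on their own and be made aware of their preferred type and perspective of motor imagery". It neither includes nor excludes controls by name.

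On recording, C.3.8 has trainees keep a log and report it by telephone, then adds: "However, there will not be a direct exercise follow-up". No log or question about imagery use is described for controls. C.3.9 analyses participants with follow-up data in the groups to which they were assigned.

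**The concern.** Group 3 is the only arm without a programme, so it is the only reference for the effect of training as such. C.2 wants that effect on autonomic functions (aim 1) and on imagery ability, where "the effects of the mentioned training program on the motor imagery skills of individuals will also be examined" (aim 2). If controls can take the tested content home during the same two weeks, the reference is no longer reliably untreated.

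Two features make this hard to repair afterwards. Download is by choice, so the controls who use the content are self-selected. And since no record of control use is described, the analyst could neither measure the exposure nor carry out a sensitivity analysis for it. The pilot is also meant to inform a full-scale study, and a control condition described in two ways cannot be carried forward cleanly.

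**Working it through.** The protocol gives no figure for control uptake, so there is none to reproduce. The check is a comparison of the texts, followed by a conditional calculation of what uptake would do.

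**Texts side by side**

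1. *What controls may receive.* C.3 allows the same content on request. C.3.8 allows no special application. The two fit together only if access comes after the second evaluation, and that condition is not written.
2. *Introductory session.* The sentence follows the list of all three groups, which suggests that everyone attends. Yet C.3.8 then uses the word participants for people who, after the familiarisation training, receive videos made for their group. That suggests Groups 1 and 2 only. The text does not settle it.
3. *Analysis.* Under C.3.9 a control who used the content remains in the control arm. That is the right rule for an analysis by assignment, but it means the exposure passes into the estimate.

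**Effect on the contrasts**

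Let c be the fraction of controls who use a programme and respond as fully as trainees. Both c and the full response are assumptions.

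- *Same programme as the comparison arm.* With a training effect d, the control mean moves by c × d. The contrast becomes d − c × d = (1 − c) × d. At an assumed c = 0.20 (3 of the 15 controls per group targeted after losses), it is 0.80 × d.
- *Opposite programme, autonomic outcome.* Suppose, as an assumption, that activating imagery moves a measure by +d and relaxing imagery by −d. If c of the controls use the relaxing content, the control mean moves by −c × d. Activating versus control becomes d + c × d = (1 + c) × d, or 1.20 × d at c = 0.20. The contrast is inflated, not diluted.
- *Equal split under the same assumption.* The control mean moves by (c/2) × d − (c/2) × d = 0, and neither contrast changes on average.
- *Imagery ability.* Both programmes practise kinesthetic imagery, so both can be expected to move it the same way. The (1 − c) case is then the likely one, with bias toward zero.
- *Group 1 versus Group 2.* The control mean does not enter this contrast, so c has no effect on it.

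**The case against.** The strongest reply is that the download sentence may not describe access during the trial at all. The English is evidently translated, the bracketed word for control sits awkwardly, and the operational account in C.3.8 gives controls only a reminder call. Deferred access may have been intended, or the bracket may be a slip. This is plausible and lowers confidence that any control would in fact be exposed. It does not remove the point: staff following C.3 could release the link in the first week, and either explanation requires the sentence to be corrected.

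Three stronger readings may tempt a reader, and the protocol does not support them.

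- *That all three groups are trained in imagery and urged to practise.* C.3.8 can equally be read as confining the session to Groups 1 and 2. If it was meant for everyone, it is a shared run-in: the contrast would then estimate the added effect of the two-week programme, which is a legitimate design choice.
- *That every contrast with control shrinks toward zero.* With two programmes that may act in opposite directions, shrinkage is only one case for the autonomic outcomes.
- *That the required sample size rises by a known factor.* One could scale the 63 per group planned for a full-scale study by 1/(1 − c)², but no uptake is given and the same-programme, full-response case need not apply. The pilot's 15 per group rests on rules of thumb, not on power.

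It is also fair that the feasibility limits in C.3.7 (dropout not above 20%, session participation not below 70%) do not depend on the control contrast.

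**Conclusion.** The concern holds as a contradiction with a real consequence. C.3 permits controls to have the tested content with no timing limit, C.3.8 says they receive no special application, and C.3.9 keeps any user in the control arm. Followed as written, the plan can bias the only comparisons with an untreated group. The bias would probably be toward zero for imagery ability and of unknown direction for autonomic outcomes. The head-to-head comparison of the two programmes stands.

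Its size cannot be stated from the protocol. The factor 0.80 illustrates one case, resting on an assumed 20% uptake, use of the same programme as the comparison arm, and full response. Contamination is a risk built into the wording, not something shown to occur. The ambiguity over the introductory session is secondary, and the point does not depend on it. What an arm receives, and when, is a matter for the protocol itself, so it cannot be left to a statistical analysis plan.

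**What to change.** Reconcile C.3 and C.3.8 as follows.

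1. State in C.3 that the download opens to controls only after their second evaluation, and which programme or programmes it contains.
2. State in C.3.8 whether the introductory session and the encouragement to practise are for Groups 1 and 2 only or for all groups. If for all, say that the contrast with control estimates the added effect of the two-week programme over that session.
3. At the second evaluation, ask every control whether they used imagery content and which, and report the answers alongside the analysis by assigned group.

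The cost is a change of wording, a delayed link and one question at an existing visit. Controls who want the content wait about two weeks for it.

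### The protocol allocates by simple randomisation in two places and by matching to Group 1 in a third, and gives no procedure that reconciles them

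*Protocol*

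**What the plan says.** Three places in the protocol describe how the groups are formed.

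- Section C.3, Randomization: "Participants will be divided into three groups using a simple randomization method based on a single sequence using computer software". A researcher who takes no part in evaluation or treatment does this.
- Section C.3.8: "In this study, participants will be randomly assigned to one of three groups".
- Section C.3.5, which deals with the controls, states: "Participants to be included in Group 2 and Group 3 will be matched by age, gender and dominant hand with those in Group 1". No age tolerance, matching ratio or order of recruitment is given.

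On numbers, section C.3 (Sample size) cites 12 per group as the minimum for a pilot study and sets a target of 15 per group. It then plans 54 participants, 18 per group, to allow for possible losses of 20%. The feasibility paragraph in section C.3.7 treats 20% as the highest acceptable dropout.

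Section C.3.9 analyses continuous outcomes by a two-factor mixed ANOVA, with group as the between-participant factor and time as the within-participant factor. It has no term for matched sets. Its intention-to-treat statement relies on the group to which each person was first assigned.

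**The concern.** Under simple randomisation, each assignment is independent of the participant's characteristics and of who is already in Group 1. Matching Groups 2 and 3 to Group 1 requires the opposite: who enters those groups depends on age, gender and hand, given the make-up of Group 1. One team following C.3 and C.3.8 and another following C.3.5 would run different studies from the same document.

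The first aim in section C.2 is to examine the two imagery programmes and compare them with each other, so the way the groups are formed carries the main inference. If people were placed to match, the groups could be balanced on the three named factors but would lose the protection of random allocation on everything else. If the matching sentence were ignored, simple randomisation of only 54 people would leave arm sizes to chance, although the sample size paragraph assumes 18 in each. Neither problem can be repaired after enrolment.

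**Working it through.** **Inputs.** Target 15 per group, 20% losses, 18 per group, 54 in total, and 12 as the cited pilot minimum (all from section C.3, Sample size). Simple randomisation from a single sequence (section C.3, Randomization). Two assumptions are mine: the sequence is 54 independent draws with probability 1/3 for each arm, and losses are independent between participants at 10% or 20%.

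**The plan's own figure.** 15 × 1.2 = 18 per group, and 18 × 3 = 54. This reproduces.

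**Step 1: the passages side by side.** C.3 and C.3.8 make assignment independent of characteristics; C.3.5 makes it depend on three of them. The two could be joined by forming triplets alike in age, gender and hand and randomising within each triplet. That is not simple randomisation from one sequence, the protocol does not describe it, and the C.3.9 model has no term for triplets.

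**Step 2: arm sizes at allocation.** With N = 54, the sizes (a, b, c) follow a multinomial distribution:

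P(a, b, c) = 54! / (a! b! c!) / 3^54

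- Each arm has mean 54/3 = 18 and SD √(54 × 1/3 × 2/3) = √12 = 3.46. The central 95% range is 11 to 25.
- P(18, 18, 18) = 54! / (18!)³ / 3^54 = 0.0151, or 1.5%.
- Summing over all outcomes with a smallest arm below 15: 0.454, or 45%.
- Smallest arm below 12: 0.080, or 8.0%.
- Largest minus smallest arm at least 6: 0.624, or 62%.
- Expected smallest arm 14.5; expected gap between largest and smallest 7.2.

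**Step 3: evaluable participants after losses.** With retention r, an arm of size k yields Binomial(k, r) evaluable participants.

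For arms fixed at 18, P(some arm below 12) = 1 − [P(Bin(18, r) ≥ 12)]³:

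- r = 0.9: 1 − 0.99883³ = 0.0035, or 0.4%.
- r = 0.8: 1 − 0.94873³ = 0.146, or 15%.

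For simple randomisation, the same product is averaged over the multinomial in Step 2.

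| Loss | Some arm below 12 evaluable, simple randomisation | Same, arms fixed at 18 |
|---|---|---|
| 10% | 23% | 0.4% |
| 20% | 52% | 15% |

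**The case against.** Several points on the other side have force.

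- **Matching and randomisation are not incompatible in principle.** A reader might infer that the two can never be combined, or that neither method could give 18 per group. The first fails because triplets can be randomised within set; the second because complete 1:1:1 matching would equalise the arms. What stands is narrower: the text contradicts itself, and the procedure that would join the two is missing.
- **Bias is not shown to occur.** A reader might infer that staff will pick people for Groups 2 and 3 and that the between-group tests are therefore invalid. No section says this, and giving allocation to an uninvolved researcher points the other way. The risk is conditional on C.3.5 being carried out by placement.
- **The single sequence might be a list with 18 slots per arm.** That would remove the arm-size figures. The protocol does not say so, the word simple points to independent draws, and such a list would still not produce matching.
- **Unequal arms cost little precision.** Averaged over the possible allocations, the variance of a pairwise contrast rises by about 4%, with about 25% at the 95th percentile. Unequal size alone causes no bias. This stands.
- **Chance imbalance in sex or age is partly absorbed.** In a group-by-time analysis of pre and post data, stable differences in level cancel. Imbalance matters there only if those factors modify the change, which the document does not address. I place no weight on imbalance.
- **Fixing arms at 18 does not secure 15 evaluable.** At 20% loss the expected number is 18 × 0.8 = 14.4. Some arm then falls below 15 with probability 1 − 0.501³ = 87%, against 97% under simple randomisation. Restricted randomisation protects the minimum of 12 far better than the target of 15.

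**Conclusion.** The point holds as a contradiction in the allocation rule. Sections C.3 and C.3.8 randomise without regard to characteristics, C.3.5 matches on three of them, and nothing in the protocol reconciles the two. This should be settled before anyone is allocated, because the between-group comparison depends on it.

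The arm-size result is secondary and rests on reading the sequence as 54 independent draws. On that reading the planned 18 per group is met exactly with probability 1.5%, and some arm starts below 15 with probability 45%. The figures for fewer than 12 evaluable rest further on independent losses. They run from 23% at 10% loss to 52% at 20%, which is the plan's own allowance and upper limit.

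The documents do not support a finding that the trial is non-randomised or that its tests are invalid. They support only that one of the allocation statements, if followed, would make it so.

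**What to change.** Delete the matching sentence in C.3.5. In C.3, replace simple randomisation with concealed 1:1:1 permuted-block allocation, with block sizes 3 and 6 in random order, stratified by gender and produced by the same independent researcher. In C.3.9, add gender and age as covariates in the between-group model, and dominant hand for the hand-laterality outcome, so that all three factors named in C.3.5 are still addressed.

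If the sponsor prefers to keep matching, form triplets on age (with a stated tolerance), gender and hand, randomise within each triplet across the three arms, and reflect the triplets in the C.3.9 analysis. With all 54 enrolled in 18 complete triplets this gives 18/18/18, but it requires enough similar volunteers to complete each set.

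The cost is protocol wording and a different computer-generated list. Blocks are slightly more predictable than simple randomisation, which varying the block size and concealing the list limit. Incomplete blocks in the gender strata may leave arms one or two away from 18.
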